#### 2.7.2. Secondary Measures

Socio-demographic data: The participants will complete a questionnaire about their age, gender, educational level, marital status, living unit and health information.

Risk of falling: The Fall Risk Index questionnaire (FRI-21) will be administered. It is a 21-item instrument that assesses both the internal and external factors present in the risk of falling. Each item is scored as 1 (risk) or 0 (no risk), with higher scores implying a greater falls risk. A 9 to 10 cut-off point is considered suitable for the early detection of fall risk [55].

Fear of falling: The Falls Efficacy Scale-International (FES-I), developed by the ProFaNE, will be applied. It is a 16-item self-report instrument that collects information on concerns about falls in a variety of daily activities, with excellent reliability and validity values (intraclass correlation coefficient = 0.96) [56,57]. Its score consists of a 4-point scale (from 1, “slightly worried”, to 4, “very worried”).

Number of falls: The number of falls suffered by participants in the last three and six months, and the last year, will be recorded. However, only the outcomes for the last three months will be used to analyze the effect of the intervention, while the falls in the last six months and the last year will only be used to characterise the sample.

Physical fitness:The 2-min walk test assesses the longest distance in metres that a person can walk along a rectangular path. It has high reliability, and its intraclass correlation coefficient is 0.888 [58].Lower body strength: The 30-s Chair Stand Test will be performed, which consists of sitting down and standing up from a chair for 30 s, counting the repetitions that the person can perform. Its reliability is considered high (0.87) [59].Lower limb flexibility: This will be measured by performing the Sit and Reach Test. Participants will sit with one leg extended and then slowly bend over, sliding their hands down the extended leg trying to touch (or pass) the toes of the toe line. The number of centimetres before reaching (negative score) or beyond (positive score) the toe will be recorded [60]. Two attempts will be measured for each leg. The average of the best results of both legs will be considered for the analysis. Its intraclass correlation coefficient value is 0.92, which shows high reliability [61].Speed: The Brisk Walking Test will be performed. The time taken to cover 30 m walking will be considered. Two repetitions will be conducted, with a one-minute rest between them [62], taking the best repetition for the analyses. The test–retest reproducibility of this assessment is 0.95, and its Cronbach’s alpha coefficient of reproducibility is 0.96 [63].The Short Physical Performance Battery (SPPB) consists of three direct observation tasks: walking speed, balance, and the time taken to get up five times from a chair [64]. The Cronbach’s alpha value is 0.70 [65].Self-perception of physical fitness: The International Fitness Scale (IFIS) [66] will be administered. It permits us to obtain information about the participants’ general physical fitness self-perception, as well as their cardiorespiratory fitness, strength, speed-agility, and flexibility. This scale is composed of five questions with five response options (“very bad”, “bad”, “average”, “good” and “very good”).

Health-related quality of life: The Short Form-12 (SF-12) questionnaire will be used. This tool has eight elements (physical function, physical role, bodily pain, general health, vitality, social function, emotional role, and mental health), and two short components, physical and mental. The score ranges from 0 to 100 (0 being the worst and 100 being the best status). The SF-12 allows us to obtain the quality-adjusted life-years of life SF-6D [67,68].

Cognitive function: The Montreal Cognitive Assessment (MoCA) will be applied. It is a screening test for cognitive impairment that assesses eight cognitive domains (attention, executive functions, numeracy, language, working memory and recall, abstraction, orientation, and visuospatial processing) [69].

Safety: A log will be kept for each of the sessions in which any incident, injury or problem that arises will be noted, recording the possible origin of the problem.

Applicability: The percentage of participants who carry out the programmed activities will be calculated. If an individual is not able to carry out the activities, the reason will be indicated.

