**Abstract:**

Approximately one-third of elderly people aged over 65 who live in the community experience falls every year, with the proportion increasing with age. Moreover, of those who fall, about half will fall again in the following year. The falls’ consequences include disability, morbidity, and mortality. Although many external and internal factors lead to falls, balance issues play a major role. Multi-component training programs (McTP) usually combine balance, strength, cardiorespiratory fitness, and flexibility, with studies reporting multiple benefits on the health-related quality of life. Halo Sport is a transcranial direct-current stimulation (tDCS) device with promising results for gait performance. This study aims to test the effectiveness of the introduction of a tCDS device to an McTP to prevent falls in older adults. The sample will consist of 46 people aged 65 years or older, randomly assigned to experimental (n = 23) and control (n = 23) groups. The experimental group will perform the McTP while wearing tDCS, and the control group will perform McTP without the device, for three sessions per week over 12 weeks. The main measures will provide information about (1) safety, (2) applicability, (3) balance, (4) number of falls, (5) physical fitness, (6) risk of falling, (7) fear of falling, (8) health-related quality of life, and (9) cognitive function. Among the practical implications of this program, it is intended to provide data on its safety and effectiveness to be implemented in different resources as a tool for the prevention of falls.

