### 2.4. Randomization and Blinding

After the initial assessment, a simple computer-generated randomisation sequence will be generated to assign the participants (1:1) to the experimental (McTP + tDCS) and control (McTP) groups using Research Randomizer software (Version 4.0, Geoffrey C. Urbaniak y Scott Plous, Middletown, CT, USA; http://www.randomizer.org, accessed on 15 September 2021) [46]. A researcher not involved in the study will prepare the randomization sequence. This information will be hidden in a password-protected file. Both the participants and professionals who will lead the sessions will be aware of their group allocation; however, it will be hidden from the data analysis investigators.

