### 2.6. Intervention

#### 2.6.1. The Multicomponent Exercise Program

Before starting the first training session, the participants will receive an explanation of the protocol to follow. The program will be composed of 3 sessions (30 min) per week over 12 weeks. Each session will be supervised by experts in the field. The structure of the sessions will consist of a 10-min warm-up (joint mobility, stretching), a 20-min main part of McTP exercises or activities wearing the Halo, and a 10-min cool-down (stretching, final thoughts and personal hygiene). The participants will wear the Halo only during the main part (20 min). The McTP will consist of balance, strength, cardiorespiratory endurance, and flexibility exercises, with several of these components being trained in each session. Examples of the activities are provided in Table 1. Furthermore, each participant will be asked for the Rating of Perceived Exertion [49] at the end of each session in order to monitor the intensity of the session.

The McTP includes gradual increases in exercise intensity, volume and complexity, together with accompanying balance, strength, endurance and flexibility exercises [25]. 

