#### 2.6.3. Control Group

Participants will perform the McTP program without the tDCS stimulation. 

Both the experimental and control groups will participate in the initial, mid-term and final evaluations.

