## Figures and Tables

**Table 1 biology-11-00290-t001:** Examples of the activities and exercises performed according to the physical abilities in the multi-component training programme.

Physical Ability	Examples
Balance	Exercises on one foot, tandem or semi-tandem position. Exercises in movement walking with heel to toe support. Line walking. Multidirectional movements with extra weights. Altering the base of support. Modified Tai Chi exercises.
Strength	Free weights. weight-bearing exercises. Machines exercises. Pilates.
Cardiorespiratory endurance	Walking indoors and outdoors. Treadmill walking. Stationary cling. Climbing steps/stairs.
Flexibility	Stretches. Yoga.

**Table 2 biology-11-00290-t002:** Schedule of the evaluations in the experimental and control groups.

Measures	Week 0	Week 6	Week 12
Sociodemographic data	√		
Balance	√	√	√
Number of falls (a) last year (b) last 6 and (c) 3 months	√	√	√
Physical fitness	√	√	√
Fall Risk	√	√	√
Fear of falling	√	√	√
Health-related quality of life	√	√	√
Cognitive function	√	√	√
Security	√		√
Applicability	√		√

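### The three-month falls recall does not fit visits six weeks apart: at week 6 at least half of the look-back lies before randomisation

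*Protocol article*

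**What the plan says.** All references are to the protocol article.

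- **Recall periods (section 2.7.2):** "The number of falls suffered by participants in the last three and six months, and the last year, will be recorded". The two longer periods serve only to describe the sample; for the treatment comparison, "only the outcomes for the last three months will be used to analyze the effect of the intervention".
- **Visits (Table 2):** the row "Number of falls (a) last year (b) last 6 and (c) 3 months" is ticked at weeks 0, 6 and 12. Section 2.6.3 adds: "Both the experimental and control groups will participate in the initial, mid-term and final evaluations".
- **Programme (section 2.6.1):** "The program will be composed of 3 sessions (30 min) per week over 12 weeks".
- **Randomisation (section 2.4):** it follows the initial assessment, so all time before week 0 is pre-randomisation.
- **Analysis (section 2.8):** a repeated-measures ANCOVA, adjusted for age and the baseline value, is applied across the dependent variables, with time and group-by-time effects reported. The same section describes the baseline covariate in terms of pre-post comparisons.

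Nothing gives the week-6 visit a shorter look-back, leaves its falls count out of the analysis, or says how overlapping look-backs are handled.

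**The concern.** A recall question measures a treatment effect cleanly only if its look-back lies within the time on treatment. Here the look-back is about twice the spacing of the visits. The week-6 count therefore mixes falls that the device could have influenced with falls that happened before anyone was allocated. Falls shortly before baseline enter both the baseline covariate and the week-6 outcome, and falls early in the programme are counted at week 6 and again at week 12.

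At stake is how the falls result can be read. The week-6 group contrast would be muted. A change between weeks 6 and 12 could also reflect nothing more than the window moving forward over treated time. This is settled at data collection: if the week-6 question asks only about three months, no later analysis can separate falls in weeks 0 to 6 from earlier ones.

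**Working it through.** The plan gives no figure for falls. Its one calculation, for TUG, can be reproduced. The SD of change is 1.3 × √(2 × (1 − 0.7)) = 1.007. A difference of 0.97 at two-sided 0.05 and 80% power then needs 17 per group, and 17/0.8 = 21.25, rounded up to 22, or 44 in total. None of this depends on falls.

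**Inputs.** Visits at t = 0, 6 and 12 weeks (Table 2). Randomisation just after week 0 (section 2.4). Look-back L of three months (section 2.7.2), taken as 52/4 = 13 weeks, or 12 weeks if a month is read as four weeks. Each count covers the interval from t − L to t.

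| Quantity | L = 12 weeks | L = 13 weeks |
|---|---|---|
| Week-6 look-back before randomisation | 6/12 = 50% | 7/13 = 54% |
| Week-12 look-back before randomisation | 0/12 = 0% | 1/13 = 8% |
| Weeks shared by the week-0 and week-6 counts | 6 | 7 |
| Weeks shared by the week-6 and week-12 counts | 6 | 7 |
| Weeks shared by the week-0 and week-12 counts | 0 | 1 |

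**Dilution.** Assume a constant fall rate and an effect that is complete from the first day. Before randomisation the two arms have the same expected rate; afterwards the ratio is RR. The apparent rate ratio is then:

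- week 6: (7 + 6RR)/13, or (6 + 6RR)/12 for the shorter reading;
- week 12: (1 + 12RR)/13, or simply RR for the shorter reading.

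The week-6 count therefore shows 6/13 = 46% to 6/12 = 50% of the true relative reduction. As arithmetic only, not as an expected effect, RR = 0.50 would appear as (7 + 3)/13 = 0.77 (or 0.75) at week 6, and as (1 + 6)/13 = 0.54 (or 0.50) at week 12.

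**Group-by-time.** With a weekly rate λ, the expected group difference in counts is 6λ(1 − RR) at week 6 and 12λ(1 − RR) at week 12. It doubles although the effect is constant, so part of any interaction comes from the window.

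**Sparsity.** The abstract says "Approximately one-third of elderly people aged over 65 who live in the community experience falls every year". Taking one-third per year at a constant hazard, the 12-week risk is 1 − (2/3)^(12/52) = 8.9%, and 23 × 0.089 is about 2 fallers per arm. This is a general community figure applied to people who will all be exercising, so it shows scale only. Most values would be zero, which a normal-theory ANCOVA describes poorly.

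**The case against.** The strongest reply is that the protocol never says outright that the week-6 falls count is an effect outcome. A three-month recall nearly matches a 12-week programme, and the pre-post wording in section 2.8 can be read as week 0 against week 12. On that reading the overlap is 0 to 1 week, which is negligible. A tick in Table 2 shows collection, not analysis: the same row also ticks the six-month and one-year recalls after baseline, which section 2.7.2 uses only for description. This stands as far as it goes and makes the dilution conditional. It does not remove the point, because the repeated-measures model with group-by-time makes use of week 6 the natural reading, and nothing excludes it.

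Several stronger conclusions are tempting but not supported:

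- **That the week-6 count is mostly pre-randomisation.** It is 54% on one reading and exactly half on the other; at least half is what can be said.
- **That shared falls bias the comparison or invalidate its standard errors.** Pre-randomisation falls are balanced between arms in expectation, and a repeated-measures model is meant to handle correlated counts within a person. The overlap dilutes and adds noise; it does not favour an arm.
- **That the fall reductions quoted in the Introduction size the loss.** Those come from exercise programmes, and here both arms exercise. The document gives no falls effect for adding the device.
- **That low power for falls is itself a fault.** Falls are secondary and the trial is sized on TUG.
- **That the Discussion claims fall prevention and must be cut.** Its wording is prospective and conditional.

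**Conclusion.** The point holds as a mismatch between recall period and visit spacing for a secondary outcome. The overlap follows directly from the stated schedule: at week 6, 50% to 54% of the look-back precedes randomisation, adjacent counts share 6 to 7 weeks, and week 12 carries 0 to 1 pre-randomisation week. The consequence is conditional. If week 6 is analysed, its contrast shows roughly half of the true relative reduction, assuming a constant rate and an immediate effect. If only week 12 is analysed, the loss is trivial, but the unsuitable model for sparse counts remains. The primary TUG analysis and the sample size are not touched, so the trial does not stand or fall on this. It is worth correcting because the change is small and the week-6 information cannot be recovered afterwards.

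**What to change.** 1. At weeks 6 and 12, ask for the number of falls since the previous assessment, giving counts for weeks 0–6 and 6–12. No fall is then counted twice, and no post-baseline count contains pre-randomisation time.
2. Keep the three-month, six-month and one-year recalls at baseline only, to describe the sample and supply a covariate.
3. Define the falls outcome as total falls per person over weeks 0–12.
4. Take falls out of the common ANCOVA. Use a simple count model, for example Poisson with robust standard errors and log time at risk as offset, with an exact method if an arm has no falls. Report the rate ratio with 95% CI as descriptive.

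If three-month data have already been collected, the minimum is to state that only the week-12 count is used for the treatment comparison and to acknowledge the 0 to 1 week of overlap.

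The existing safety record ("A log will be kept for each of the sessions in which any incident, injury or problem that arises will be noted") should not replace the visit question. As described it covers session incidents rather than falls at home, and section 2.4 says that session leaders know the allocation.

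**Cost.** One reworded question, one corrected table row and a different model for one outcome. The downside is that the on-programme count is no longer directly comparable with the three-month baseline recall, so a raw before-after change in falls cannot be quoted.

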We aim to study whether the association of a multi-component training program (McTP) combined with transcranial direct-current stimulation (tDCS) device (Halo Sport) is safe, applicable, and can enhance performance on gait and balance. Additionally, this project has a secondary aim to evaluate the effect of the combined program on the falls, physical fitness, health-related quality of life, and cognitive function of participants, and the safety and applicability of the program. We hypothesize that the group that performs the McTP combined with tDCS will obtain better results in the primary variable, balance, as well as in the secondary variables.

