### 2.3. Sample Size

The sample size was estimated based on the Time Up and Go (TUG) test results in older people, a test which is considered valid and reliable for this population [43,44]. Thus, accepting a risk alpha of 0.05 and a risk beta of 0.2 in a bilateral contrast, a total of 44 individuals (22 both in the experimental and control group) are needed in order to find a difference equal to or higher than 0.97 units. A common standard deviation of 1.3 and a correlation coefficient between the baseline and end-line measurement of 0.7 are assumed [45]. A loss of follow-up rate of 20% is predicted.

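### Safety is part of the main aim, but it rests on a passive session log that Table 2 does not match and that does not prompt for non-fall problems between sessions or after stopping

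*Protocol article*

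**What the plan says.** The Introduction asks whether the combined programme "is safe, applicable, and can enhance performance on gait and balance". The same paragraph repeats under the secondary aim "and the safety and applicability of the program" and names balance as the primary variable. The Abstract puts safety first in its list: "The main measures will provide information about (1) safety, (2) applicability, (3) balance".

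The method is given in section 2.7.2, under Secondary Measures: "A log will be kept for each of the sessions in which any incident, injury or problem that arises will be noted", together with the possible origin of the problem. The Applicability entry that follows says the reason will be given when someone cannot carry out the activities. The falls entry in the same section collects falls by recall.

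Table 2 ("Schedule of the evaluations in the experimental and control groups") has columns for weeks 0, 6 and 12. Its Security row is ticked at weeks 0 and 12 and empty at week 6. The Applicability row has the same pattern. Falls are ticked at all three times.

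Section 2.4 places allocation after the baseline visit: "After the initial assessment, a simple computer-generated randomisation sequence will be generated". It also says that participants and session leaders know the allocation, while the analysts do not.

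**The concern.** A trial that sets out to say whether an added device is safe depends on how problems are found. Two features of the text raise doubt.

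First, section 2.7.2 and Table 2 describe different things. A log kept at each session is continuous recording; two ticks at assessment visits look like a two-point measurement, and one of those points comes before anyone has been exposed. Staff following the table and staff following the text could collect different data.

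Second, the log is passive. It notes what arises and prompts nobody. A problem that starts after the participant goes home enters only if someone happens to mention it later. Because leaders and participants know who wears the device, the readiness to mention or to write down a problem may differ between the arms. Events that were never collected cannot be recovered at the analysis stage.

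**Working it through.** The point rests on no figure in the plan, so the check is mainly a comparison of passages.

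**Step 1: timing.** Section 2.4 puts randomisation after the initial assessment, so week 0 in Table 2 comes before allocation and before the first session. A safety entry at week 0 can be a baseline or mark the start of recording; it cannot hold an event related to the intervention.

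**Step 2: number of recording occasions.** Section 2.6.1 states: "The program will be composed of 3 sessions (30 min) per week over 12 weeks". That is 3 × 12 = 36 sessions, so up to 36 log occasions per participant under section 2.7.2, against 2 ticks in Table 2. The article does not connect the two.

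**Step 3: which events have a stated route into the data?**

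| Type of event | Stated route |
|---|---|
| Problem during a session, including in someone who later drops out | Session log, up to the last session attended |
| Fall, wherever it happens | Falls recall at weeks 0, 6 and 12 |
| Problem that keeps someone from the activities | Reason recorded under Applicability, not linked to the safety log |
| Non-fall problem that begins between sessions, participant continues | No stated prompt; may be volunteered at the next session, or picked up at week 12 if that tick means an enquiry |
| Non-fall problem that begins after the participant stops | No stated route, unless it can be picked up at a week-12 assessment |

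The last two rows are the gap.

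**Step 4: how many could miss the week-12 assessment?** Section 2.3 says: "A loss of follow-up rate of 20% is predicted". Applied to the 46 participants in the Abstract, 0.20 × 46 = 9.2, so about 9. This counts people who may lack a week-12 entry. It does not count people without safety data, because their session log runs to their last session.

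**Step 5: symmetry between arms.** Both groups attend the exercise sessions, and the log is not restricted to one group, so both can be logged. What is not stated is a common prompt, in a trial where leaders and participants know the allocation.

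**The case against.** The strongest reply is that little is actually lost. The log runs at every session, three times a week, so attendees are seen every few days and nothing in the sentence bars a problem reported at the next session. Falls, an important harm in this population, are collected separately. The reason for not carrying out activities is recorded. The Security ticks share their pattern with Applicability, which accumulates over the programme, so both may simply mark the start and end of continuous recording. Definitions and follow-up of adverse events may be in the full protocol, which is not shown. Safety also appears under the secondary aim and among the secondary measures.

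Much of this stands, and it rules out several stronger readings:

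- A reader might infer that participants who drop out leave no safety record. The session log and the Applicability entry contradict that.
- A reader might infer that safety is measured only at two visits. The per-session log contradicts that too.
- A reader might compare session time with all the hours in 12 weeks and treat the ratio as the share of events seen. That assumes a problem is recorded only if it occurs during a session, which the text does not say.
- A reader might argue that one or two missed events would change the conclusion. The article states no safety threshold or decision rule, so there is no basis for this.

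Two things remain. The start-and-end reading of Table 2 is possible but unstated. And the possibility that a problem is volunteered at the next session is not a prompt; with open allocation, relying on volunteering is weaker than asking everyone the same question.

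**Conclusion.** The concern holds in a limited form. The table and the text are not reconciled, and read naturally neither provides for non-fall problems that begin between sessions or after a participant stops. This affects an outcome named in the main aim, and such data cannot be reconstructed later, so it is worth correcting before the trial relies on it.

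The size cannot be given as a number of missed events. The only figure available is the roughly 9 of 46 participants who might lack a week-12 assessment, on the assumption that the predicted 20% loss applies to everyone randomised.

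It would go too far to say that the result is biased towards safety. Incomplete capture can lower the count, but the effect on the comparison is unknown: session leaders might note more problems in device users because they are watching for them, or fewer. The conclusion assumes that the log is filled in from what arises or is volunteered, and that the full protocol adds no between-session enquiry.

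**What to change.** 1. Reconcile Table 2 with section 2.7.2: show safety as recorded at every session, first to last, in both arms. If the week-0 and week-12 ticks are kept, state what is collected at each.
2. At each session, ask every participant in both arms the same question about any problem since the previous session, and enter the answer in the existing log.
3. Copy the reason already collected under Applicability, when someone cannot carry out or stops the activities, into the safety record.

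The cost is one corrected table row and a little existing staff time. Prompting will probably bring in more minor events, in both arms, and the report should say that they were elicited by a standard question. A problem that begins after someone stops, and was not the reason for stopping, may still be missed; the report should say so. None of this changes the intervention or its schedule.
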